### Primary study parameter

The flexion angle of the TKA in the sagittal plane is measured to determine difference in femoral component placement between the groups. This angle is commonly defined as the angle ‘*γ*’ between the bone stub axis (BSA) of the femur [25] and the neutral line of the femoral component of the prosthesis [12] (Fig. 3). Due to artifacts in the fluoroscopic assessment caused by the metal in the prosthesis, the neutral line is unidentifiable. However, the most anterior plane on the inside of the femoral component of the prosthesis, the frontal flange, can be detected in the fluoroscopic assessment (Fig. 3). Therefore, the angle ‘*θ*’ between the frontal flange and the BSA is measured. The angle between the frontal flange and the neutral line is 97°; thus, the formula *γ* = *θ* − 7° can be used for future comparison between gamma and theta measurements. To obtain the angle ‘*θ*’, the BSA is aligned with the vertical *y*-axis by coronal and sagittal rotating the 3D volume image. Furthermore, the transversal plane is rotated towards an anatomic orientation to correct any femur rotation deviations from acquisition. The latter is necessary to be able to compare different cases. Once the orientation of the femur is standardized within the 3D volume image, the frontal flange can be manually annotated and compared with the *y*-axis, the BSA. For annotation, the sagittal slice with the most prominent frontal flange is chosen and to minimize measurement error from manual annotation an average over 5 iterations is used. We hypothesize that the flexion angle will be larger in the flex rod group (i.e., better fit to the distal anatomy of the femur, Fig. 2).

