#### Statistical analysis

Sagittal flexion angle of the TKA will be reported as mean and standard deviation (or median and interquartile range (IQR)). An independent two-sample *t* test (or non-parametric equivalent) will be used to analyze the effect of group (flex rod versus standard rod). All secondary outcome parameters will be reported as mean and SD (or median and IQR). Repeated mixed model analysis techniques will be used to analyze the effects of group, time, and their interaction. All other study parameters will be reported as mean and standard deviation (or median and IQR). Independent *t* tests (or non-parametric equivalent) and Chi square (in case of frequencies) will be used to analyze the effect of group. All statistical analyses will be performed using Stata/IC for Windows, Release 13 (StataCorp LLC, College Station, TX, USA).

The sample size calculation is based on the primary study parameter: flexion angle of the prosthesis in the sagittal plane. Our hypothesis is that this angle at 3 months will be smaller in the standard rod group compared to the flex rod group. First, the flexion angle in posterior stabilized TKA has been reported to be about 6° [1]. Second, the mean intra-observer difference between measurements for this angle is 2.3° with an estimated standard deviation of 5° [16]. We assume that a clinical relevance of a mean difference of 5° between the rod groups can be measured [21], but this will be further studied in our study. Using G*Power (version 3.1.7 [11]), a sample size was calculated for an independent two-sample *t* test, with the variables *m*1 = 6°, *m*2 = 11°, *σ*1 = 5°, *σ*2 = 5°, *α* = 0.05, and power = 0.80. This calculation yielded a sample size for the total group of *N* = 54, with 27 for each group. Taking into account a drop out of participants during the course of the study of 10%, a sample size of *N* = 60 subjects is needed, with 30 subjects in each group.

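### The 5° SD in the sample size is sourced to repeat readings by one observer, but the t test needs the spread across patients; name its source and restate the power that 27 per group gives

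*Protocol article*

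**What the plan says.** All of the sizing is in the second paragraph of Statistical analysis in the protocol article.

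- Endpoint: "The sample size calculation is based on the primary study parameter: flexion angle of the prosthesis in the sagittal plane", taken at 3 months.
- Test: "a sample size was calculated for an independent two-sample *t* test", with group means of 6° and 11°. The mean of about 6° has its own citation, given without an SD.
- Difference: "We assume that a clinical relevance of a mean difference of 5° between the rod groups can be measured".
- SD: the only sentence that gives a spread for this angle reads "the mean intra-observer difference between measurements for this angle is 2.3° with an estimated standard deviation of 5" degrees. The calculation then enters 5° as the SD of each group.
- Result, at alpha 0.05 (sidedness not stated) and power 0.80: "This calculation yielded a sample size for the total group of *N* = 54, with 27 for each group". This is raised to 60 for 10% dropout.

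Two other places bear on the point. Under Primary study parameter, the angle comes from manual annotation of the frontal flange, and "to minimize measurement error from manual annotation an average over 5 iterations is used". The Discussion says that reliability and validity have not yet been established for the in-house measurement software.

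**The concern.** A two-sample t test compares the difference in means with the variation of the endpoint among patients in the same arm. That variation has two parts: true differences between patients in how the component sits, and whatever measurement error remains in each patient's recorded angle. A repeat-reading statistic describes the second part only. The article's own rationale makes the first part matter, because the Background says that sagittal bowing varies between people and the flexible rod is meant to follow it.

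The SD is a central input to the trial's only sample size calculation. If its origin is the wrong quantity, the stated power rests on a figure that was not estimated for the purpose. A reader cannot tell whether 5° is a between-patient SD, a reading-error SD or a working assumption.

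**Working it through.** **Inputs.** From Statistical analysis: difference Δ = 11° − 6° = 5°; SD σ = 5° in each group; alpha 0.05; power 0.80; 27 per group evaluable; 10% dropout. Two-sided alpha is my assumption, because the article does not state it.

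**Step 1. Reproduce the plan's own figure.** The standardised difference is d = Δ/σ = 5/5 = 1.0. The normal approximation is n = 2(z₀.₉₇₅ + z₀.₈₀)²/d² = 2(1.960 + 0.842)² = 15.7, so 16 per group. The exact calculation uses the noncentral t distribution with 2n − 2 degrees of freedom and noncentrality d√(n/2). It gives:

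| Target power | Two-sided, n per group | One-sided, n per group |
|---|---|---|
| 0.80 | 16.7, so 17 | 13.1, so 14 |
| 0.90 | 22.02, so 23 | 17.8, so 18 |
| 0.95 | 26.99, so 27 | 22.4, so 23 |

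The stated 27 per group does not follow from power 0.80. It equals the two-sided result for power 0.95. Allowing for a rank test at 80% power does not explain it either: 16.7/0.955 = 17.5 and 16.7/0.864 = 19.3, so 18 to 20 per group. The dropout step is correct: 54/0.9 = 60.

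**Step 2. Power of the planned trial over a range of SDs.** No between-patient SD is given, so the total SD (patients plus residual error) is varied. These values are assumptions. Δ = 5°, two-sided alpha 0.05:

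| Total SD | d = 5/SD | Power at 27 per group | n per group for 80% |
|---|---|---|---|
| 4° | 1.25 | 0.995 | 12 |
| 5° | 1.00 | 0.95 | 17 |
| 6° | 0.83 | 0.85 | 24 |
| 6.4° | 0.78 | 0.80 | 27 |
| 7° | 0.71 | 0.73 | 32 |
| 8° | 0.63 | 0.62 | 42 |

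**Step 3. The SD that the trial tolerates.** With 27 per group, the smallest d detectable at 80% power is 0.777, so the limit is 5/0.777 = 6.4°. If all 30 per group are evaluable, it is 5/0.736 = 6.8°.

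**Step 4. Why the direction of any error is open.** Suppose that 5° is the SD of the difference between two readings with equal, independent errors. One reading then has error SD 5/√2 = 3.54°. The total SD for a single reading is √(between² + 12.5). It equals 5° when the between-patient SD is √(25 − 12.5) = 3.54°, and lies below 5° for smaller values and above it for larger ones. The article gives nothing that places the trial on either side.

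**The case against.** The strongest reply is that the sentence is loosely built and that 5° was meant as the SD of the angle itself. The figures leave room for this. If 2.3° is a mean absolute difference between readings, normal errors centred on zero imply an SD of signed differences of 2.3 × √(π/2) = 2.9°. The SD of the absolute differences would be √(2.88² − 2.3²) = 1.7°. Neither is near 5°. A signed mean of 2.3° with SD 5° is possible, but it would mean that one observer shifted systematically on re-reading. This stands as a reason for caution. It does not settle the matter, because the cited source is not at hand and the sentence does not say that 5° is a spread across patients.

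A second reply is that an article condenses the full protocol, which may hold a proper source. That also stands. But the article does state a provenance, and as printed it is a different quantity. If a better source exists, naming it closes the point.

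A third reply is that the sample size has slack. This is correct and softens the consequence: 27 per group keeps at least 80% power up to a total SD of about 6.4°. The slack exists only because the stated power and the stated N disagree, so it cannot be cited until the two are reconciled.

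A reader might infer that 5° is too small and the trial underpowered, or that it cannot say whether it can detect 5°. The documents support neither, because the true SD is unknown in both directions and the tolerance can be stated. Nor can the averaging of five annotations be turned into a figure for residual error. It is described only for the annotation step, made after the femur has been oriented, and independence of the five readings is not established.

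**Conclusion.** The point holds as a fault in how the SD is justified. The only origin given for 5° is an intra-observer repeat-reading statistic, the test needs the spread across patients, and no source for that spread appears in the article.

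It does not hold as a claim of inadequate size. At 27 per group, power for a 5° difference is about 0.95 if the total SD is 5°. It reaches 0.80 at about 6.4° and falls to 0.73 at 7° and 0.62 at 8°. These figures assume two-sided alpha 0.05, equal SDs in the two arms and 27 evaluable per arm. The SD values themselves are assumptions.

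The stated power of 0.80 is inconsistent with 27 per group on the article's own inputs, which need 17, and must be corrected with the SD.

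**What to change.** 1. State what the 5° is the SD of. If a between-patient source exists, cite it; if not, call 5° an assumption.
2. Separate the intra-observer figure from the group SD in the text, so that reading error is not taken for variation among patients.
3. Reconcile power with N. Say that 27 evaluable per group gives about 0.95 at SD 5°, and add sidedness. Then give the short table (0.95 at 5°, 0.85 at 6°, 0.80 at 6.4°, 0.73 at 7°, 0.62 at 8°) and say that at least 80% power holds up to a total between-patient SD of about 6.4°.

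N stays at 60. The cost is a few sentences and one small table. The downside is that the stated power becomes conditional on an assumed SD, no longer one fixed value.

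### The stated sample-size inputs give 34 patients, not 54; with 27 per group the power on those inputs is 0.95, not 0.80

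*Protocol article*

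**What the plan says.** The calculation is in the Statistical analysis section of the protocol article and is based on the primary parameter, the sagittal flexion angle. The article says that "a sample size was calculated for an independent two-sample *t* test", run in G*Power 3.1.7. The inputs are group means of 6° and 11°, an SD of 5° in each group, alpha 0.05, "and power = 0.80". The 5° difference is the one treated as clinically relevant: "We assume that a clinical relevance of a mean difference of 5° between the rod groups can be measured". The output is given in the next sentence: "This calculation yielded a sample size for the total group of *N* = 54, with 27 for each group". Attrition is then added: "Taking into account a drop out of participants during the course of the study of 10%, a sample size of *N* = 60 subjects is needed", that is, 30 per group.

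The article does not say whether the test is one- or two-sided, although the hypothesis is directional: "Our hypothesis is that this angle at 3 months will be smaller in the standard rod group compared to the flex rod group". The calculation mentions no adjustment for multiplicity, for a non-parametric test or for any other design feature.

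**The concern.** A difference equal to one SD is large, and 27 per group is far more than 80% power usually requires for it. Every input the calculation needs is printed next to its result, so the figure should be reproducible from the page, and it is not.

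This is the only justification of the sample size, and it concerns the primary outcome. As printed, it tells the reader that the trial accepts a 20% chance of missing a 5° difference. It also leaves unexplained why 20 more evaluable patients are sought (54 − 34) than the stated requirement calls for. A reader judging how well the design would withstand an SD above 5° would start from the wrong power.

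**Working it through.** **Inputs** (all from the Statistical analysis section): m1 = 6°, m2 = 11°, σ1 = σ2 = 5°, alpha = 0.05, power = 0.80, equal groups, independent two-sample t test, 10% dropout. Sidedness is not stated, so both cases are computed.

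**Effect size.** d = (11 − 6)/5 = 1.0.

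**Formula.** With n per group, the test statistic follows a noncentral t distribution with 2n − 2 degrees of freedom and noncentrality d·√(n/2). Two-sided power is the probability that it falls beyond ± t(0.975; 2n − 2). One-sided power uses t(0.95; 2n − 2) in the upper tail only.

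**Attempt to reproduce 27 per group at power 0.80**

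| n per group | N | Two-sided power | One-sided power |
|---|---|---|---|
| 14 | 28 | 0.721 | 0.824 |
| 16 | 32 | 0.781 | 0.868 |
| 17 | 34 | 0.807 | 0.886 |
| 26 | 52 | 0.942 | 0.972 |
| 27 | 54 | 0.9501 | 0.976 |
| 30 | 60 | 0.968 | 0.985 |

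The smallest n for 0.80 is 17 two-sided and 14 one-sided. The normal approximation gives 16 and 13. None of these is near 27. For n = 27 the noncentrality is √13.5 = 3.674 and the two-sided critical value on 52 degrees of freedom is 2.007, which gives power 0.9501. Because 26 per group gives only 0.942, 27 is exactly the two-sided solution for power 0.95.

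**Dropout step.** 54/0.9 = 60, as stated. The same step from 34 gives 34/0.9 = 37.8, so 38. The discrepancy therefore arises before dropout is applied.

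**Other explanations, two-sided at power 0.80**

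- *Non-parametric test.* The section allows a non-parametric equivalent. Inflating 17 by an asymptotic relative efficiency of 0.955 gives 17/0.955 = 17.8, so 18 per group. The worst-case efficiency of 0.864 gives 17/0.864 = 19.7, so 20 per group.
- *Stricter alpha.* Alpha 0.01 gives 26 per group, which is close but not 27, and nothing in the text suggests it.
- *One-sided testing.* This lowers the required n and widens the gap.

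**What 27 per group would support at 80% power.** Solving the two-sided power equation at n = 27 for 0.80 gives d = 0.777. With SD 5° this is a difference of 0.777 × 5 = 3.9°. With a difference of 5° it is an SD of 5/0.777 = 6.4°.

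**The case against.** The strongest reply concerns attribution. The arithmetic shows that the inputs and N disagree, but it does not prove that power is the misreported entry. Other combinations also give 27 per group:

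- two-sided alpha 0.025 with power 0.90;
- two-sided alpha 0.05/6 with power 0.80;
- power 0.90 with the SD enlarged by the quoted 2.3° intra-observer difference, √(25 + 2.3²) = 5.5°;
- power 0.80 with an SD of about 6.4°.

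This point stands as a limit on diagnosis, and it means 0.95 should not be written in without checking. It does not rescue the text. Each route changes at least one stated input and none is documented. Whichever entry was wrong, the two-sided power at 27 per group on the inputs as printed is 0.950. Changing power alone to 0.95 is the simplest single correction that reproduces the figure.

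The second reply is that the error is harmless. On the stated assumptions the trial has more patients than 80% power needs, no estimate is biased, the analysis is unaffected and recruitment need not change. That is true, and it limits the damage to reporting. It does not make the statement correct.

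It is also fair to say that the document never describes the extra patients as a safeguard against a larger SD. They do provide such headroom, but no intention should be read into it.

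**Conclusion.** The concern holds: the stated power and the stated sample size cannot both be right. At power 0.80 the stated inputs require N = 34 (38 after 10% dropout), against 54 and 60 as printed. At 27 per group the two-sided power is 0.950, and at 30 per group it is 0.968. The type II error at 5° is therefore 5% with 27 per group, where the text implies 20%.

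These figures assume two-sided testing, equal groups and a true SD of 5°. One-sided testing makes the mismatch larger. They do not establish that the SD really is 5°. With 27 per group and a 5° difference, power falls to about 0.85 at an SD of 6° and 0.73 at 7°.

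The statement has to be corrected because it is the sole justification of the sample size and is wrong on its face. The error is conservative and gives no reason to change the target of 60.

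**What to change.** Retrieve the original G*Power output and report the inputs actually used, including whether the test was one- or two-sided. Keep N = 60.

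- **If the output shows power 0.95:** replace the sentence with, for example: *For a difference of 5°, an SD of 5° in each group, two-sided alpha 0.05 and power 0.95, 27 patients per group (N = 54) are required, or 60 after allowing for 10% dropout.*
- **If the output shows power 0.80 with another input different from the text:** state that input. For N = 54 at two-sided alpha 0.05, it would have to be an SD of about 6.4° with the 5° difference, or a difference of about 3.9° with the 5° SD. These values should be stated only if they were the planning assumptions. They should not be back-calculated to fit, and 3.9° would also depart from the 5° the article calls clinically relevant.
- **If the output cannot be found:** say so, and report that 27 per group gives two-sided power of 0.95 on the stated difference, SD and alpha.

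The cost is one corrected sentence, with no change to recruitment, conduct or analysis.

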## Discussion

This randomized controlled trial has been set up to assess how the use of a flex rod affects the fit of the TKA and if this results in better functional outcome. As the sagittal fit of TKA is not a standardized outcome measure, we chose to define the fit with two outcome measures: the first being the flexion angle of the femoral component. It is expected that the flexion angle will be larger in the flex rod group as the femoral component is expected to have a better fit to the distal anatomy of the femur. The second outcome measure is the contour of the distal femur, quantified in the anterior sagittal profile and the posterior sagittal profile at various positions. It is expected that for the flex rod group, due to smaller sizing of the femoral component, the distal anatomy of the femur with TKA will be closer to the pre-operative distal anatomy. We expect that this will be most apparent in the anterior profile where the effect of overstuffing after use of the standard rod is expected to be largest [17]. Also, for this reason, patients in this trial will receive a posterior stabilized TKA, standardizing the posterior placement of the femoral component (in contrast to a cruciate-retaining TKA), and with differences in the anterior part of the distal femur as the only degree of freedom.

Custom-made software is used for calculating the parameters of sagittal fit of the TKA. Due to the unavailability of existing software for measuring the specific parameters for the specific model of TKA, this software was produced in-house. The advantages of this software is that it is tailored made for the study-specific parameters. Disadvantages of this software are that currently we have no data on the reliability and validity of the measurements and that by using imaging of the knee, it is unable to account for articular cartilage thickness [20]. During the TKA procedure, the cartilage of the different cuts will be scored. Using this information, the measurements of the sagittal profile can be corrected for cartilage thickness of 0, 1, and 2 mm, with the values based on the literature [20]. Other parameters that are measured during the TKA procedure are the sagittal thickness (in millimeters) of the cuts, and the area of the cuts. It is expected that due to a better fit of the femoral component to the distal anatomy in the flexible IM rod group, less bone has to be cut, resulting in lower thickness and smaller area of these cuts.

We expect that the use of the flex rod will result in an overall better functional outcome. This is supported by Hitt et al. [17], who studied patient and clinician reported outcome measures in a RCT. The modeling study by Marra et al. [24] showed that such effects may be explained by the increase in the patellar tendon moment arm. Our aim is to study the effects of a flex rod in a prospective RCT combining imaging, surgery details, functional outcome, and patient-reported outcomes, thus providing a data set on which our hypotheses can be thoroughly tested.

## Data Availability

Not applicable.

## Abbreviations

ADL: Activities of daily living
BSA: Bone stub axis
IQR: Interquartile range
PCO: Posterior condylar offset
PCOi: Intersection of the posterior condylar offset of the distal femur in the sagittal plane
PTA: Patellar tendon angle
RCT: Randomized controlled trial
TKA: Total knee arthroplasty
